**Figure 1 F1:**
[figure not shown]
Flow chart of the project procedure. *Measurements obtained which do not belong to Care As Usual (CAU) of the Pain Rehabilitation Department of the Center for Rehabilitation of the University Medical Center Groningen (CvR–UMCG). CLBP, chronic low back pain; CSI, Central Sensitisation Inventory; HRV, heart rate variability; PDI, Pain Disability Index; QST, quantitative sensory testing; Rand36-PF, Rand36 Physical Functioning subscale; VAS, Visual Analogue Scale; WAS, Work Ability Score.

During the first appointment of the patients with the rehabilitation physician, patients are invited to participate in the studies if based on their file they are eligible according to the criteria defined for the studies. Eligible patients who are invited to participate and receive information about the study, but have not reacted, are contacted in a week’s time to remind them about the study participation. Those who sign the informed consent, fill in forms with their relevant personal information during the baseline assessment and are given vouchers for the travel expenses during the discharge assessment. Participating patients follow CAU trajectory with the Pain Rehabilitation team in terms of assessments, screening and implementation of the interdisciplinary rehabilitation programme. As part of the research protocol, the performance of additional assessments and filling up of questionnaires on CS and functioning are required. CSI, lifting capacity and HRV results are collected as CAU. Aerobic capacity, QST, objective PA monitoring, and pain intensity and functioning questionnaires’ results are collected as additional to CAU. All CS measurements, objective PA monitoring and capacity tests are measured at two time points, baseline and discharge. Pain intensity and functioning questionnaires, on the other hand, are measured at 13 time points, baseline and once a week during the 12-week rehabilitation programme. Pain Disability Index (PDI) is the only functioning questionnaire collected as CAU at baseline but as additional during the rehabilitation programme. A diagram of the project procedure is presented in figure 1.

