### Sample size

Due to the limited amount of relevant previous or similar studies, the sample sizes for the several analyses described in this research protocol are estimated a priori with GPower (G*Power for Windows, Version 3.1.9.2), and are exploratory as a result.

The following sample size calculations, as well as the planned statistical analyses later described, will be performed with proxies for the main variables. Additionally, due to the influence of patient’s sex and age in the assessment outcomes, all analyses will include these variables for a moderator effect.

*Sample size for objective 1: to analyse the association between instruments assessing reference symptoms and signs attributed to CS.* Correlation analyses will be performed for this objective. The correlation between the different CS measurements is expected to be weak as reported on associations between certain CS measures and tests.^24^ For a correlation coefficient of 0.25, an α error probability of 0.05 and a power of 0.8, a minimum sample size of 97 is calculated.
*Sample size for objective 2: to analyse whether reference symptoms and signs attributed to CS are associated with functioning measurement outcomes; and for objective 3: to analyse whether changes (between baseline and discharge) in reference symptoms and signs attributed to CS are related to changes in each of the functioning measurement outcomes*. Multiple regression analyses will be performed for objectives 2 and 3. Based on the associations between CSI and psychosocial and cognitive behavioural factors,^24 25^ the effect size is hypothesised to be medium. Since minimally three CS measurements are tested with sex and age required as independent variables, and controlled for the confounding effect of other demographic and test-related variables, eight predictors are foreseen. Taking into account the factors mentioned above, the sample size calculation results in a minimum of 77 patients, calculated with an α error probability of 0.05 and a power of 0.8. Finally, patients measured at discharge could be about 30% less than at baseline due to either not following the interdisciplinary rehabilitation programme or personal reasons; a sample size of 110 patients may be required in this scenario.

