The presence of missing data will be checked. If a variable has more than 10% of missing data cases, its distribution will be further examined. When the distribution of missing data is missing completely at random, analyses with pairwise deletions are planned. If data are not missing completely at random, other suitable solutions will be applied such as multiple imputation.^91^ Regarding the presence of outliers, cases at 3 SD from the mean will be considered as outliers. Their influence will be measured using Cook’s distance and leverage values. When the outliers are not statistically influential and/or there is rationale for the outlier, no further actions are planned. The descriptive statistics of the sample characteristics and main test results will be at this point calculated; numerical variables as mean and SD in normally distributed data and as median and IQR (25–75)) in non-normally distributed data, and categorical variables as counts and percentage of each category level.

*Statistical approach for objective 1: to analyse the association between instruments assessing reference symptoms and signs attributed to CS.* Multiple partial correlation analyses will be performed and corrected for potential confounders. CS measurements will be the main variables and sex and age will be covariates. Additional covariates may enter the partial correlations based on their correlation coefficient with CS instruments and if p<0.01. Results will be reported as correlation coefficients (Pearson’s r and/or Spearman’s rho) and p values, with and without controlling for covariates. The significance level for all analyses is established at 0.01, to account for the potential type I error due to the multitude of partial correlation analyses.
*Statistical approach for objective 2: to analyse whether reference symptoms and signs attributed to CS are associated with functioning measurement outcomes.* First, multiple correlation analyses, followed by multiple regression analyses with data obtained at baseline, will be performed. Each of the main outcomes from functioning measurements will be introduced in the models as dependent variable, CS measurements as independent variables, and sex, age and other demographic characteristics and/or test-related variables as potential confounders and/or moderators.

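### For objective 3, deletion rests on judging data missing completely at random, a check with about 48% power at 0.4 SD; change slopes and correlations may be attenuated

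*Protocol article*

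**What the plan says.** The Analyses section sets a three-step rule. First, a trigger: "If a variable has more than 10% of missing data cases, its distribution will be further examined". Second, the default: "When the distribution of missing data is missing completely at random, analyses with pairwise deletions are planned". Third, the alternative: "If data are not missing completely at random, other suitable solutions will be applied such as multiple imputation". It names no test, significance level or set of comparison variables for the judgement, and it does not describe the imputation model.

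The Sample size section anticipates the largest block of missing data: "patients measured at discharge could be about 30% less than at baseline due to either not following the interdisciplinary rehabilitation programme or personal reasons". It gives no split between the two reasons. For that case it adds that "a sample size of 110 patients may be required in this scenario".

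Under Procedures, the CS measures, accelerometry and capacity tests are taken at baseline and discharge only. The pain-intensity and functioning questionnaires, by contrast, "are measured at 13 time points, baseline and once a week during the 12-week rehabilitation programme". Objective 3 correlates and regresses change in functioning on change in CS measures, using baseline-to-discharge differences.

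**The concern.** The expected loss of about 30% exceeds the 10% trigger, so the rule will come into play for the discharge values, and with them for the delta scores of objective 3. A patient not measured at discharge has no delta on any measure taken only twice. For those variables, pairwise deletion amounts to analysing completers.

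The rule treats missing completely at random as the state that licenses deletion. Data can contradict that state, but failing to contradict it in a small sample does not establish it. The protocol also gives a reason for doubt: some of the loss comes from not following the programme, which could plausibly be related to how a patient is responding. If patients who are not improving leave more often, the remaining sample is selected partly on the dependent variable of the change models. The delta-on-delta slopes and correlations are then pulled towards zero.

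**Working it through.** **1. The plan's own figures.** The Sample size section states: "the sample size calculation results in a minimum of 77 patients, calculated with an α error probability of 0.05 and a power of 0.8". It has eight predictors, of which three are CS measures, and "the effect size is hypothesised to be medium". I take medium as f² = 0.15 (an assumption). For the F test of three of eight predictors, N = 77 gives λ = 0.15 × 77 = 11.55 on 3 and 77 − 9 = 68 degrees of freedom, with power 0.80. So 77 reproduces. Allowing for 30% loss, 77 / 0.70 = 110, which also reproduces. The split is therefore 77 completers and 110 − 77 = 33 dropouts.

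**2. Power of the check.** Assume a two-sample t test at two-sided 0.05 on one baseline variable, since no test is named.
- Standard error of the standardised difference: √(1/77 + 1/33) = 0.208.
- For an assumed difference of 0.4 SD: noncentrality 0.4 / 0.208 = 1.92 on 108 df, power 48%.

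| Difference (SD) | Power |
|---|---|
| 0.2 | 16% |
| 0.3 | 30% |
| 0.4 | 48% |
| 0.5 | 66% |
| 0.6 | 82% |

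Eighty per cent power needs about (1.96 + 0.84) × 0.208 = 0.58 SD. At alpha 0.01, power at 0.4 SD is about 25%. An omnibus chi-square over k independent variables, one of them shifted by 0.4 SD (noncentrality 0.4² × 77 × 33 / 110 = 3.70), has power 33%, 27% and 20% for k = 3, 5 and 10.

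**3. What deletion does to the change slope.** These are large-sample simulations with 30% logistic dropout. All settings are assumed.

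*Mild selection* (dropouts and completers about 0.41 SD apart on the driver, true slope 0.36 in absolute value, baseline–discharge correlation 0.6):

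| Dropout driven by | Change in slope |
|---|---|
| Baseline CS | 0.1% |
| Baseline functioning | 0.6% |
| Change in CS (the predictor) | 0.0% |
| Change in functioning | about 3% attenuation |
| Change in both | about 4% attenuation |

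*Dropout driven by a mid-programme score* correlating 0.7 with final change in functioning, true slope 0.36 or 0.46: attenuation of 1–2%, 5–6% and 12–13% for weak, moderate and strong dependence.

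*A separate simulation, also driven by poor mid-programme change*, true slope 0.46–0.47:

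| Analysis | Weak | Moderate | Strong |
|---|---|---|---|
| Deletion | 0.45 | 0.42 | 0.40 |
| Imputation, baseline data only | 0.45 | 0.43 | 0.40 |
| Imputation plus one mid-programme score | 0.46–0.47 | 0.46–0.47 | 0.46–0.47 |

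The strong case is (0.47 − 0.40) / 0.47 = 15%. The middle case is (0.46 − 0.42) / 0.46 = 9%, larger than the 5–6% above. The labels weak, moderate and strong are not calibrated to each other or to any figure in the protocol.

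**4. Correlations and explained variance.** These can shrink even when the slope does not. With dropout driven only by the predictor, R² fell by about 3% (mild) to 12% (moderate).

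**5. Pairwise deletion itself.** At n = 77 with 10–30% missing per variable and data truly missing completely at random, interval coverage was about 95%. The issue is possible bias when that condition fails, not the standard errors.

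**The case against.** The case for leaving the rule alone has real force.

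- **The plan already provides for imputation** when data are not missing completely at random. That stands. The weakness is the gate, not the absence of a method.
- **Power and bias concern different mechanisms.** The 48% is for a baseline difference, whereas the slope bias comes from dropout linked to change during the programme. Missing a 0.4 SD baseline difference does not itself bias the slope; in the simulation the effect was under 1%. This stands. It also means that a baseline comparison sees change-driven dropout only as far as change correlates with baseline.
- **Imputing from baseline data alone barely helps** (0.45 / 0.43 / 0.40 against 0.45 / 0.42 / 0.40). This stands too. The content of the imputation model matters more than which branch is taken.
- **Several variables could be checked one by one.** With seven, one of them shifted by 0.4 SD, the chance of at least one flag is 1 − (1 − 0.478) × 0.95⁶ = 62%. But with no shift at all it would be 1 − 0.95⁷ = 30%, so this gate discriminates poorly.
- **The bias is modest beside sampling error.** On standardised scores the slope's standard error at n = 77 is about √((1 − 0.46²) / 75) = 0.10, more than the largest shift of 0.07. That limits the severity. It does not justify keeping the rule, because attenuation does not average out.

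A reader might also infer more than the protocol supports. It does not attribute the whole 30% to the programme: personal reasons are the stated alternative. It does not say that the fallback would leave out the weekly scores, because it is silent on the imputation model. And mean improvement, which change-driven dropout would overstate among completers, is not an objective 3 result. That objective concerns associations between changes.

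**Conclusion.** The point holds as a weakness in how the method is chosen. With 77 completers and 33 dropouts, an assumed two-sample check at 0.05 has about 48% power for an assumed 0.4 SD difference, and 16% to 82% over 0.2 to 0.6 SD. Not rejecting missing completely at random is thus weak support for deletion.

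The consequence is conditional. If dropout depends on change in functioning, the objective 3 slopes and correlations may be attenuated. For slopes the size is about 2–6% under weak to moderate dependence on mid-programme change (about 9% in one moderate setting) and about 12–15% under strong dependence. If dropout depends only on the model's predictors, the slope is not biased.

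It would be tempting to conclude that the change analysis is biased as planned. The documents do not support that: they do not say that leaving depends on outcome, and every dropout mechanism above is assumed. The change should be made, but the flaw does not invalidate the study.

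**What to change.** For objective 3, remove the choice that depends on judging the data missing completely at random. State multiple imputation under missing at random as the main analysis. Include the baseline CS and functioning measures and the weekly Rand36-PF, PDI, WAS and VAS Pain scores as auxiliary variables. Report complete-case results alongside as a sensitivity analysis.

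The cost is some extra analysis work; the method is already named in the plan and no new data collection is needed. The limits should be stated with it:

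- Results will depend on the imputation model.
- The gain is largest for Rand36-PF, the only one of the four functioning proxies collected weekly. It is smaller for lifting capacity, aerobic capacity and accelerometry, which, like the CS measures, are taken only twice.
- Patients who never start the programme may have no weekly scores.
- The full recovery of the slope in the simulation reflects dropout driven by the very score that was added. Dropout depending on unobserved values would remain uncorrected.

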### Analyses

Data records from the different tests and questionnaires will be collected and merged into one database. The database management will be done by the project team and handled according to the internal regulations of the UMCG. The analyses of the study will be performed with SPSS software version 22.0 (IBM).

Before any analysis, data will be prepared:

Variables need to be calculated: body mass index; DMA, WUR and CPM tests (see the Methods and analyses section, Measurements: CS measurements); PDI, Rand36-PF, PCS, BSI and IEQ questionnaires.HRV: data will be preprocessed to correct for any artefacts that may be present at the beginning or at the end of the recording.QST: the overall value of each sensory test is the mean at the most painful location and the five control locations together, provided that at most two locations are missing.To perform the analyses to respond to objective 3, delta scores are computed (difference in scores between baseline and discharge) for CS, functioning and those confounder variables which are also measured at the same time points as the main measurements.

Proxies of the main measurements were selected to perform analyses. CS variables are: the sum score of CSI part A and the RMSSD for HRV. For QST, no variables are predefined, variables that correlate most strongly with each of the functioning measures will be selected. Functioning variables are: the maximal weight lifted for lifting capacity, the VO_2_max/kg for the maximal aerobic capacity, the daily vector magnitude (VM) counts for PA and the average score of Rand36-PF for reported physical functioning.

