*Statistical approach for objective 3: to analyse whether changes (between baseline and discharge) in reference symptoms and signs attributed to CS are related to changes in each of the functioning measurement outcomes.* A similar approach to objective 2 will be performed: first, multiple correlation analyses will be performed with data obtained at baseline and discharge, followed by multiple correlation analyses using delta scores of the data and, finally, multiple regression analyses again using delta scores. As in objective 2, each of the main outcomes from functioning measurements will be introduced in the models as dependent variable, CS measurements as independent variables, and sex, age and other demographic characteristics and/or test-related variables as potential confounders and/or moderators.

Confounders entering the final models of objectives 2 and 3 will be selected based on their partial correlation coefficient with CS and functioning, and they will be included if p≤0.10. All multiple regression models will have the assumptions checked. Results of objectives 2 and 3 will be reported as coefficient (b), CIs (95% CI), p values and explained variance, with and without controlling for confounders and/or moderators. Due to the large amount of correlation analyses and the risk of high type I error, a stricter significance level for correlation analyses is established, p<0.01. For multiple regression analyses the significance level is at 0.05.

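### Influence diagnostics are reserved for cases already flagged at 3 SD, and the rationale clause can leave an explained influential value untouched; the effect is probably minor

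*Protocol article*

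**What the plan says.** The outlier rule stands in the Analyses section of the protocol article, after the missing-data text and before the statistical approach for each objective. It has three steps, of which the first two run together.

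- Screen and influence: "cases at 3 SD from the mean will be considered as outliers. Their influence will be measured using" Cook's distance and leverage. For the screen, neither the variable nor a residual is named. For the influence step, the possessive refers back to the cases just defined as outliers.
- Action: "When the outliers are not statistically influential and/or there is rationale for the outlier, no further actions are planned".

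Two other sentences in the same section bear on the point. For the regressions of objectives 2 and 3: "All multiple regression models will have the assumptions checked". Influence is not mentioned there. For artefacts: "HRV: data will be preprocessed to correct for any artefacts that may be present at the beginning or at the end of the recording". The article states no comparable step for sensory testing, the exercise test or accelerometry.

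**The concern.** Cook's distance and leverage are meant to find cases that look ordinary on each variable but unusual in combination. A patient with a high CS score and surprisingly good lifting capacity, each perhaps 2.5 SD from its mean, is an example. Placing a distance-from-the-mean screen in front of these diagnostics removes such cases before the diagnostic can see them. The order of the two steps is the problem; the tools themselves are suitable.

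The action clause raises a second difficulty. A rationale may mean that a patient is genuinely extreme, or that the recording is known to be faulty. The first value should stay and the second should not, yet the clause treats both alike.

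At stake is how far a CS coefficient depends on one or two patients. The regressions are sized at a minimum of 77 patients with eight predictors and are tested at 0.05, so single cases carry some weight.

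**Working it through.** **1. The plan's own figure.** The outlier rule contains no number to reproduce beyond 3 SD, but the regression sample size fixes the setting. The Sample size section gives eight predictors, at least three of them CS measurements, α 0.05, power 0.8 and an effect of which it says "the effect size is hypothesised to be medium". Taking medium as f² = 0.15 (an assumption; the article gives no number), the F test of 3 predictors out of 8 at N = 77 has λ = 0.15 × 77 = 11.55 on 3 and 77 − 8 − 1 = 68 degrees of freedom. Its power is 0.800. Allowing for 30% loss, 77 / (1 − 0.30) = 110. Both stated figures reproduce.

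**2. Which cases reach the influence check.** 3,000 data sets per scenario were simulated with eight predictors (one binary). The three CS predictors had joint f² = 0.15, so each coefficient was √0.05 = 0.224. A case counted as screened if |z| ≥ 3 on any predictor or the outcome. Cook's distance is Dᵢ = rᵢ²hᵢ / [k s²(1 − hᵢ)²], with k = 9 coefficients including the intercept. The cut-off 4/n is an assumption: 4/77 = 0.052 and 4/110 = 0.036.

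| Data | N | Cases with D>4/n per model | Of these, inside 3 SD | Most influential case inside 3 SD |
|---|---|---|---|---|
| Normal | 77 | 5.05 | 92.0% | 82.2% |
| Normal | 110 | 6.60 | 91.0% | 78.1% |
| t5 | 77 | 5.31 | 62.8% | 33.3% |
| t5 | 110 | 6.87 | 61.0% | 23.1% |
| Two log-normal predictors | 77 | 5.05 | 79.3% | 58.7% |
| Two log-normal predictors | 110 | 6.64 | 78.3% | 53.0% |

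Separate runs at N = 77 gave 60% to 62% for t5. Another set-up with log-normal predictors gave about 43%. The skewed figure is the least stable, because it depends on how many predictors are skewed and how strongly. Adding a 3 SD residual screen to the variable screen lowers the missed share by only about 1 to 3 points.

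**3. Stricter cut-offs.** In 2,000 data sets per scenario at N = 77:

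- t5, D>0.5: 101 cases, of which 3 lay inside 3 SD (3/101 = 3%).
- t5, D>1: 17 cases, none inside 3 SD.
- Normal, D>0.5: 2 cases in 2,000 models, both inside 3 SD.
- Normal, D>1: none.

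A further set of runs found none missed at either cut-off.

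**4. What one unscreened case could do.** One case was planted at +2.5 on a CS predictor and −2.5 on the outcome, and data sets were kept only where it stayed inside 3 SD on every variable (4,000 generated per N).

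- N = 77: the mean coefficient fell by 0.095 of 0.224 (42%). Significance was lost in 61% of the data sets that were significant without the case. Median D was 0.15.
- N = 110: the fall was 0.068 of 0.224 (30%), and significance was lost in 44%. Median D was 0.11.

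This shows what is possible, not how often it happens. In data with no planted case, dropping the most influential unscreened case changed significance in 3% to 9% of models in one set of runs, and in about 12% in another.

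**5. The action clause, by cell.**

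| Outlier | Read with 'or' | Read with 'and' |
|---|---|---|
| Not influential, rationale | no action | no action |
| Not influential, no rationale | no action | not settled |
| Influential, rationale | no action | not settled |
| Influential, no rationale | not settled | not settled |

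The wording allows both columns. Under the first, an influential value with a known fault gets no action.

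**The case against.** Several stronger readings are tempting, and the article does not support them.

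- *The screen is applied to one variable at a time.* This is the natural reading, since the rule speaks of distance from a mean and comes before any model is fitted. But the text does not say so, and a residual could be meant.
- *Most cases able to overturn a coefficient are never examined.* 'Most' depends on the 4/n cut-off, which is not in the article and flags about five cases per model even in clean normal data. Much of the 92% is therefore ordinary sampling variation. Under heavy tails the worst case is usually screened. 'Never' also goes too far, because the promised assumption checks could bring discordant cases to light.
- *Artefacts will stay in.* A rationale can equally mean a genuine, clinically explained value, which should be kept, and heart rate variability has its own limited correction step. The clause permits the bad outcome; it does not prescribe it.
- *A single case would change a declared correlation.* With r = 0.25 in 76 patients p is 0.029, which already fails the article's 0.01 level for correlations. An example of that kind shows nothing about this plan; only the regressions are tested at 0.05.

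It is also fair to say that numerical cut-offs, a definition of rationale and sensitivity runs are often left to a fuller document, that the study calls its sample sizes exploratory, and that coefficients and confidence intervals are reported alongside p values. Some change of significance is expected for any p value near 0.05.

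What stands is narrower. The order of the screen and the diagnostics, and the and/or clause, are stated rules rather than omitted detail, and neither the assumption checks nor the artefact step repairs them.

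**Conclusion.** The concern holds in limited form. As written, the plan does not require an influence check for a case inside 3 SD, however discordant its combination of values, and one permissible reading leaves an explained measurement fault in the analysis. The likely effect on conclusions is minor: moderately influential cases often escape the screen, but where strongly influential ones arise they are nearly all caught. The sizes rest on assumptions outside the article: f² = 0.15, the 4/n and 0.5 cut-offs, independent predictors, and normal, t5 or log-normal data. The real distributions of the delta scores and sensory ratios are unknown. The change is worth making because it is nearly free and replaces an ambiguous rule.

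**What to change.** Replace the rule with text to this effect:

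- Compute Cook's distance and leverage for every case in each final regression model, with a cut-off fixed before the data are seen.
- Correct a value, or set it to missing, only where a measurement error is documented.
- Keep all verified values, however extreme, in the main analysis.
- Report the CS coefficients with and without the flagged cases as a sensitivity analysis.

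This takes a few sentences of plan text. The software already produces these diagnostics for all cases. The downside is one extra results column. With a 4/n cut-off, about five cases per model at N = 77 should be expected there even in clean data, so that column should be read as a check on stability and not as a reason to exclude patients.

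### Explained variance is a reported result, but outcome-driven choice of the QST variable and confounders biases it upward, and adjusted R² does not remove that part

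*Protocol article*

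**What the plan says.** The Analyses section lists what will be reported for objectives 2 and 3: coefficients, 95% confidence intervals, "p values and explained variance, with and without controlling for confounders and/or moderators". It does not say whether explained variance is raw or adjusted R².

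Four other statements determine how that figure behaves.

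- **QST variable.** The CSI and RMSSD proxies are fixed. For QST none is, and "variables that correlate most strongly with each of the functioning measures will be selected" (Analyses). The Quantitative sensory testing section describes six sensory tests, and Analyses reduces each to one mean over body locations. The Discussion confirms that the choice is made separately for each functioning outcome.
- **Confounders.** They enter the final models on their partial correlation with CS and functioning, at p≤0.10 (Analyses).
- **Model size.** "minimally three CS measurements are tested with sex and age required as independent variables", and with further confounders "eight predictors are foreseen" (Sample size).
- **Numbers.** "the sample size calculation results in a minimum of 77 patients", raised to 110 because "patients measured at discharge could be about 30% less than at baseline". Objective 2 uses baseline data, so its planned number is 110. The figure of 77 is the discharge minimum for objective 3.

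**The concern.** R² never falls when a term is added, and it rises further when a term is picked because it correlates with the outcome in the same data. Adjusted R² repairs the first problem and leaves the second. The stricter 0.01 level applies only to the correlation analyses, and nothing stated corrects the effect-size estimate for selection.

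The Background gives the contribution of CS to functioning as a purpose of the study. A reader will therefore look to explained variance for how much CS matters. If the percentage includes a few points that come from choosing the best of several tests, and more from sex, age and selected confounders, that contribution will look larger than the data support.

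**Working it through.** **1. Reproduce the plan's sample size.** Inputs from Sample size: "calculated with an α error probability of 0.05 and a power of 0.8"; "the effect size is hypothesised to be medium", with no number, taken here as f²=0.15; three CS measures tested; eight predictors. Using the noncentral F with λ = f²·N and df = (u, N−p−1):

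- u=3 tested within p=8: N=77, power 0.800. This is the stated figure. (Three tested in a three-predictor model also gives 77.)
- u=8, the overall test of all eight: N=109.
- u=5 within 8: N=92.
- Allowance for loss: 77/0.70 = 110, as stated.

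The sized effect is therefore a partial R² for the three CS measures: 0.15/1.15 = 13.0%.

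**2. Null expectation with predictors fixed in advance.** For k predictors E[R²] = k/(n−1). For the partial R² of three given five others it is 3/(n−6).

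**3. Null expectation with QST selection.** Simulation with all predictors unrelated to the outcome: two fixed CS measures, one QST variable chosen as best of six (inter-test r=0.3, assumed), sex, age and three further covariates not chosen by the data. Selection and model use the same data.

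| Mean under no association | n=77 (objective 3) | n=110 (objective 2) |
|---|---|---|
| Raw R², three CS measures, fixed | 3/76 = 3.9% | 3/109 = 2.8% |
| Same, QST best of six | 6.3% | 4.4% |
| Raw R², eight predictors, fixed | 8/76 = 10.5% | 8/109 = 7.3% |
| Same, QST best of six | 12.8% | 9.0% |
| Adjusted R², eight predictors, QST best of six | 2.5% | 1.7% |
| Partial R² of CS given five others, fixed | 3/71 = 4.2% | 3/104 = 2.9% |
| Same, QST best of six | 6.6% | 4.6% |

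QST selection alone adds 6.3 − 3.9 = 2.4 points to the CS measures at n=77 and 4.4 − 2.8 = 1.6 points at n=110.

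**4. Why adjustment leaves a remainder.** Adjusted R² = 1 − (1−R²)(n−1)/(n−k−1). At n=77: 1 − 0.872 × 76/68 = 2.5%. With eight fixed predictors it averages zero, so the 2.5% is the selection effect.

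**5. Confounder selection.** The number of candidates is not stated. With 5 to 15 assumed candidates, chosen on their correlation with the outcome either at p≤0.10 or as the best three, full-model raw R² averages about 11–19% at n=77 and 8–14% at n=110. Adjusted R² averages about 4–10% and 3–7%. The partial R² of the CS measures hardly moves (about 6.4–6.8% at n=77). Confounder selection thus inflates the full-model figure, and QST selection inflates the CS figure.

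**6. How often chance reaches 13%.** At n=77 with QST selection, the partial R² of CS does so in about 7% of null samples (2% with fixed predictors), and full-model raw R² in about 44%. At n=110 the figures are about 1% and 13–14%.

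**The case against.** - **Raw or adjusted is a detail for an analysis plan.** This stands. The article's silence on it is not the finding. The selection rules are written in the article, however, and they bias either version.
- **Results are shown both ways, and no R² comparison between models is announced.** Also fair. The model without confounders shows the CS measures alone, and a rise on adding confounders would naturally be credited to them. But the CS-only model still contains the selected QST variable, and its null mean is 6.3% rather than 3.9% at n=77.
- **The null used here is too bleak.** It sets sex and age effects to zero, although the article includes them because they influence the outcomes. This stands for the full-model figures, which would not be pure chance in practice. It is also a reason not to read full-model R² as the contribution of CS.
- **The authors disclose the risk.** The strengths and limitations list says that the choice of measurements may influence results, and the sample sizes are called exploratory. Disclosure lowers the severity but does not correct the estimate.

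A reader might infer more: that chance alone yields about 13% explained variance, the very effect for which the study is sized. The documents do not support this. The 12.8% is a full-model R² at n=77, whereas 77 reproduces as a test of three CS predictors, so the 13.0% is a partial R² for those three. Its null mean is about 6.6% at n=77 even with QST selection. Nor does the 12.8% carry over to objective 2, where the full-model figure at n=110 is about 9.0%.

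**Conclusion.** The point holds as a minor one about the reported effect-size estimate. It does not touch the sample size, which reproduces. Following the stated selection rules, the variance apparently explained by the CS measures is too high by about 2.4 points at n=77 and 1.6 points at n=110 when there is no association. Adjusted R² does not remove this. The full-model figure is higher again, and outcome-driven confounder selection raises it further by an amount that depends on the unstated number of candidates.

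The size rests on these assumptions: one QST variable per outcome, chosen from six tests correlated 0.3 (uncorrelated tests give nearly the same, a partial R² of 6.8% at n=77); CS measures otherwise independent of each other and of the covariates; and selection repeated on the change scores for objective 3. The article does not say whether the QST choice is remade there. If the baseline choice were carried over, the inflation at n=77 would be smaller.

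**What to change.** State in the analysis plan that, for objectives 2 and 3:

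- explained variance is reported as adjusted R²;
- the R² increment of the CS measures over sex, age and the confounders is reported beside it, since this is the quantity closest to the sized effect;
- both carry a bootstrap optimism correction in which the QST choice and the confounder selection are repeated in every resample;
- full-model R² is not described as variance explained by CS.

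The cost is a few sentences and a short extra analysis. No data collection changes, and the reported percentages will be smaller.
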